### Eligibility and recruitment

Once potential participants are identified, inclusion and exclusion criteria will be applied. The inclusion criteria are as follows: 1) Patient over the age of 18; 2) Ability to understand and speak English; 3) Ability to understand the study protocol and able to provide informed consent; 4) Admitted to hospital and diagnosed with an acute coronary syndrome and have documented coronary artery disease on coronary angiography (coronary artery stenosis >50% in at least one coronary artery) treated either medically or with percutaneous coronary intervention; 5) Have low level of physical activity, defined by not meeting recommended weekly exercise targets 6) Personal ownership of a smartphone able to run the Fitbit application; 7) Agreement to complete cardiac rehabilitation program.

The exclusion criteria are: 1) Inability or unwillingness to provide informed consent; 2) Significant residual coronary artery disease requiring planned revascularisation; 3) Unstable angina; 4) Blood pressure > 180/110 or symptomatic orthostatic blood pressure decrease >20 mmHg; 5) Uncontrolled ventricular or atrial arrhythmias; 6) Musculoskeletal or medical problems resulting in significant exercise limitation; 7) Significant medical comorbidities with life expectancy of less than one year; 8) New York Heart Association (NYHA) Functional class III-IV; 9) Current illicit drug or alcohol use or dependence that in the opinion of the principal investigator would interfere with adherence; 10) Clinical signs of cognitive impairment. These are outline in Table 2.

**Table 2 Tab2:** Inclusion and Exclusion criteria

Inclusion Criteria
• Patient over the age of 18
• Ability to understand and speak English
• Ability to understand the study protocol and able to provide informed consent
• Admitted to hospital and diagnosed with an acute coronary syndrome and have documented coronary artery disease on coronary angiography (coronary artery stenosis >50% in at least one coronary artery) treated either medically or with percutaneous coronary intervention
• Have low level of physical activity, defined by not meeting recommended weekly exercise targets.
• Personal ownership of a smartphone able to run the Fitbit application
• Agreement to complete cardiac rehabilitation program.
Exclusion Criteria
• Inability or unwillingness to provide informed consent
• Significant residual coronary artery disease requiring planned revascularisation
• Unstable angina
• Blood pressure > 180/110 or symptomatic orthostatic blood pressure decrease >20 mmHg
• Uncontrolled ventricular or atrial arrhythmias
• Musculoskeletal or medical problems resulting in significant exercise limitation
• Significant medical co-morbidities with life expectancy of less than one year
• New York Heart Association (NYHA) Functional class III-IV
• Current illicit drug or alcohol use or dependence that in the opinion of the principal investigator would interfere with adherence
• Clinical signs of cognitive impairment

### Setting and participants

Recruitment will occur during index hospital admission at Monash Medical Centre and Dandenong Hospital, Melbourne, Australia. Melbourne is the second largest city in Australia with an estimated population of 4.5 million people with healthcare provided predominantly by a public system, with no or minimal charges to patients. Potential participants will be those admitted with an acute coronary syndrome (I.e. Unstable Angina, NSTEMI and STEMI). These patients will be screened and those meeting entry criteria will be invited to participate in the study. Once informed consent is obtained patients will undergo baseline testing prior to randomization as outlined below. Those subsequently allocated to the intervention group will receive their personal activity devices (Fitbit Charge 2) and face-to-face instruction on its proper use prior to hospital discharge.

### Device description

The Fitbit Charge 2 (Fitbit Inc., San Francisco, CA, USA) is a fitness wristband and heart rate monitor with sophisticated photo-plethysmography technology allowing heart rate derived algorithms to estimate energy expenditure based on physical activity intensity, with recent data suggesting acceptable validity [22, 34, 35]. In addition to pedometer and heart rate monitoring, the Fitbit Chargedevice has additional features of automatic activity tracking, connected GPS, automatic reminders to keep active and sleep detection technology. Fitbit Inc. as an in-kind donation will provide the device used in the study. Fitbit Inc. however, will have no involvement in the design, implementation, analysis or interpretation of the results of this study.

### Sample size required

We calculated that 152 participants (76 in both the intervention and control groups) would need to be enrolled for the study to have a statistical power of 80% to detect a clinically important increase of 25 m in the six-minute walk test [21, 22], in the intervention group as compared with the control group, with a two-sided alpha level of 0.05. Accounting for 20% loss to follow-up a minimum of 92 patients in each arm will be required. If the power was to increase to 90% at 5% level of significance 101 patients would be required in each arm of the study. We plan to recruit 100 patients in each arm, totalling 200 patients.

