### Randomization

Once all screening assessments are completed and eligibility is confirmed patients (*n* = 200) will be randomized in a 1:1 fashion to receiving the personal activity monitor (Fitbit Charge 2) in addition to usual cardiac rehabilitation or the usual cardiac rehabilitation alone through a computer based randomization process (Fig. 1). A computer-generated table will allocate patients in fixed blocks of four. In order to prevent selection bias, the allocation sequence will be concealed from the investigators enrolling and assessing patients utilizing computer randomization software.

Baseline patient demographics and pre-defined screening and assessment, including the 6-min walk test, will occur prior to randomization after patients have given informed consent. Assessors of the primary outcomes will be blinded to the treatment allocation, however participants are not able to be blinded.

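### The attrition-adjusted minimum of 92 per arm should be 95, and the 101 per arm for 90% power needs to be labelled as a figure before loss to follow-up

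*Protocol article*

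**What the plan says.** All the figures are in the section Sample size required of the protocol article, in this order.

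- Base case: "We calculated that 152 participants (76 in both the intervention and control groups) would need to be enrolled", at 80% power, "to detect a clinically important increase of 25 m in the six-minute walk test", "with a two-sided alpha level of 0.05".
- Loss to follow-up: "Accounting for 20% loss to follow-up a minimum of 92 patients in each arm will be required".
- Higher power: "If the power was to increase to 90% at 5% level of significance 101 patients would be required in each arm of the study".
- Decision: "We plan to recruit 100 patients in each arm, totalling 200 patients".

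The Randomization section adds that patients "will be randomized in a 1:1 fashion". The article gives no SD for the walk distance or its change, and no power for the planned 100 per arm.

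**The concern.** Two things stand out when the four statements are read in sequence.

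First, 92 looks like 76 increased by 20% rather than 76 divided by the 80% expected to remain. If so, the stated minimum does not do what it is said to do: a trial that enrolled 92 per arm and lost 20% would have fewer than 76 per arm to analyse.

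Second, the paragraph moves between two kinds of number without saying so. The 76 is a number to be analysed and the 92 is a number to be enrolled. The 101 comes straight after the attrition sentence but does not say which kind it is, and it is followed at once by a recruitment target of 100, which is subject to loss. A reader cannot tell from the text what power the planned size has once the plan's own loss rate is applied.

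At stake is the accuracy of the published sample-size statement, not whether 200 patients are enough for the stated 80%.

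**Working it through.** **Inputs from the section Sample size required:** 76 per arm at 80% power; difference 25 m; two-sided alpha 0.05; loss 20%; 92 per arm after loss; 101 per arm at 90% power; 100 per arm planned. Allocation is 1:1 (Randomization). The SD is not stated and is back-solved below. The calculation is taken to be a comparison of two independent means.

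**1. Reproduce 92.** 76 × 1.2 = 91.2, rounded up to 92. The multiplicative form gives the stated figure.

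**2. Test 92 against its purpose.** 92 × 0.8 = 73.6, so 73–74 evaluable per arm, below 76. The form that keeps 76 is n / (1 − loss) = 76 / 0.8 = 95, and 95 × 0.8 = 76. Put the other way, 92 tolerates a loss of only 1 − 76/92 = 17.4%. None of this needs an SD.

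**3. Is 101 before or after loss?** Under the normal approximation, with difference and SD fixed, required n is proportional to (z for alpha + z for power)². The ratio of 90% to 80% power is (1.960 + 1.282)² / (1.960 + 0.842)² = 1.339. Then 76 × 1.339 = 101.7; since 76 may itself have been rounded up from just over 75, the result lies between about 100.4 and 101.7. So 101 is the same calculation as 76, with no allowance for loss. With 20% loss it becomes 101 / 0.8 = 126.25, hence 127 per arm.

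**4. Implied SD.** Normal formula: SD = 25 × √(n/2) / (z for alpha + z for power).

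- From 76 at 80%: 25 × √38 / 2.802 = 55.0 m (54.7 m with the t distribution).
- From 101 at 90%: 25 × √50.5 / 3.242 = 54.8 m (54.5 m with the t distribution).

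Allowing for rounding of n and for either formula, SDs of about 54.3 to 55.0 m fit the plan's figures.

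**5. Power at the numbers that matter.** Two-sample calculation, 25 m, two-sided 0.05:

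| Evaluable per arm | Where it comes from | t, SD 54.5 m | Normal, SD 55.0 m |
|---|---|---|---|
| 73 | 92 enrolled, 20% lost | 78.6% | 78.4% |
| 74 | 92 enrolled, 20% lost | 79.2% | 79.0% |
| 76 | plan's base case | 80.2% | 80.0% |
| 80 | 100 enrolled, 20% lost | 82.2% | 82.0% |
| 100 | 100 enrolled, none lost | 89.8% | 89.5% |
| 101 | plan's 90% case | 90.05% | 89.8% |

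For 80 evaluable per arm, crossing every SD from 54.3 to 55.0 m with both formulas gives 81.5% to 82.9%.

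**The case against.** The case against making much of this is strong on several counts.

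- **Planned size.** The planned 100 per arm exceeds the corrected 95, leaves 80 evaluable under 20% loss, and meets the 80% target. This stands: the error has no consequence for the design.
- **The 101.** It reproduces correctly as a number before loss, just as the 76 does. This stands: 101 is not an arithmetic error. What remains is that it is unlabelled, follows the attrition sentence, and is set beside an enrolment figure.
- **Size at 92.** The shortfall is 3 patients per arm and roughly one percentage point of power. This also stands.

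One might also defend 92 on the ground that the base-case sentence speaks of enrolling 76, so that 76 is already an enrolment figure. That does not help: the next sentence adds an allowance for loss to it, which makes sense only if 76 is the number needed for analysis.

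Two stronger readings are tempting and are not supported.

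- A reader might infer that the trial claims close to 90% power because 100 stands next to 101. The sentence on 90% is conditional, the stated design power is 80%, and 100 is below even the unadjusted 101.
- A reader might infer that 92 could serve as a stopping number, because the Dissemination policy section allows completion once enough data have been collected for sufficient power. That section does not mention 92. It speaks of data collected, which points to evaluable patients, so to 76 rather than 92.

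**Conclusion.** The minimum of 92 per arm is wrong as written; under the plan's own 20% loss it should be 95, a difference of 3 per arm (6 in total). At 92 enrolled, power would be about 78–79% rather than 80%. The 101 is correct only before loss and should say so; its counterpart after loss is 127 per arm, 26 more.

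The planned 200 remains adequate for 80% power. It would stay so up to a loss of (100 − 76) / 100 = 24%. Under 20% loss its power is about 82%, and it approaches 90% only if nobody is lost.

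The 95 and 127 rest on the plan's figures alone. The power values rest on an SD that the article does not state and that is only implied by its sample sizes, but they change little over the SDs that fit. This is a correction to a stated figure and to labelling, not a fault in the size of the trial.

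**What to change.** Amend the section Sample size required as follows.

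- Replace 92 with 95 per arm (190 in total) as the number to randomise for 80% power with 20% loss.
- Describe 76 and 101 as evaluable patients per arm, and add that 101 corresponds to 127 randomised per arm (254 in total) with 20% loss.
- State that the planned 100 per arm is expected to leave about 80 evaluable, which meets the 80% target with about 82% power for a 25 m difference.
- State the SD used in the original calculation. Only the sponsor can supply it; the back-solved 54.3–55.0 m should not be written in as if it had been the plan's assumption. The 82% should be recomputed with the sponsor's SD, and until then given as 81.5–82.9% over the implied range.

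Keep 200 as the recruitment target. The cost is a text correction: no change to recruitment, budget or conduct.

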### Ethics and dissemination

This protocol and the informed consent forms were reviewed by the Monash Health Human Research Ethics Committee (HREC) with respect to the scientific content and compliance with applicable research and human subject regulations. Ethics approval was obtained with reference number LNR/17/MonH/62.

Personal health information will be collected from participants and will be stored in a secure databank. During the study a unique number will be used to identify patients with no personal information appearing on any documents or subsequent publications. The information collected will be kept in a secure location and any computer files will be password protected and retained for 15 years. Patients will have the right to access and to request correction of information held as per local state legislation.

### Randomization

Once all screening assessments are completed and eligibility is confirmed patients (*n* = 200) will be randomized in a 1:1 fashion to receiving the personal activity monitor (Fitbit Charge 2) in addition to usual cardiac rehabilitation or the usual cardiac rehabilitation alone through a computer based randomization process (Fig. 1). A computer-generated table will allocate patients in fixed blocks of four. In order to prevent selection bias, the allocation sequence will be concealed from the investigators enrolling and assessing patients utilizing computer randomization software.

Baseline patient demographics and pre-defined screening and assessment, including the 6-min walk test, will occur prior to randomization after patients have given informed consent. Assessors of the primary outcomes will be blinded to the treatment allocation, however participants are not able to be blinded.

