### Exercise prescription

Patients in both groups will be encouraged to exercise as per guideline recommendations [17] over the course of the study period. Patients in the intervention arm will be encouraged to meet a target of at least 10,000 steps per day, with the device programmed to this goal. In men who underwent an exercise rehabilitation program, improvement in walking distance (i.e. steps per day) was a strong independent predictor of survival, and a useful guide to prognosis [36] The study coordinators will be able to view these de-identified step counts in real time, however there will be no further interaction with patients in either group until the 8-week follow-up review.

The routine community cardiac rehabilitation program that all will be encouraged to attend encourages patients to engage in regular moderate intensity exercise increasing in a graded degree over a seven-week period centred around a walking program. Moderate intensity is described as exercise that is ‘neither too hard, nor too easy’, with ‘mild shortness of breath, sweating and increased heart rate’ as per the National Australian Heart Foundation recommendations [37].

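### Fixed, disclosed blocks of four can let up to a third of allocations be deduced from earlier ones, which weakens the stated concealment

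*Protocol article*

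**What the plan says.** The Randomization section states that patients "will be randomized in a 1:1 fashion to receiving the personal activity monitor" plus usual rehabilitation, or usual rehabilitation alone. It fixes the scheme: "A computer-generated table will allocate patients in fixed blocks of four". To guard against selection bias it adds that "the allocation sequence will be concealed from the investigators enrolling and assessing patients utilizing computer randomization software".

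The same section gives the blinding: "Assessors of the primary outcomes will be blinded to the treatment allocation", "however participants are not able to be blinded". Under Setting and participants, those allocated to the intervention "will receive their personal activity devices (Fitbit Charge 2) and face-to-face instruction on its proper use prior to hospital discharge". Under Exercise prescription, "The study coordinators will be able to view these de-identified step counts in real time". The planned size, under Sample size required, is: "We plan to recruit 100 patients in each arm, totalling 200 patients". Recruitment is at two hospitals, and the article does not say whether the list is stratified by hospital.

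**The concern.** Concealment has two parts: the list must not be readable, and the next entry must not be deducible. Software provides the first. A constant block size of four, printed in the protocol article, leaves the second open in a trial where one arm leaves the ward with a wrist device and the other does not. Once two patients in a block have gone to one arm, the rest of that block is settled.

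What is at stake is who enters and when. Some entry criteria call for judgement, such as whether exercise limitation is significant, or whether drug or alcohol use would in the principal investigator's opinion interfere with adherence. Someone who foresees the next arm could, without intending to, let that influence whom to approach or how such a criterion is read. The primary outcome is a change from a pre-randomization walk test, so foreknowledge could also affect how the baseline test is conducted. The plan offers concealment as its protection against this, so the weakness sits in a stated safeguard.

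**Working it through.** The plan gives no predictability figure, so there is none to reproduce. The inputs from the article are 1:1 allocation, blocks of four (two per arm) and 200 patients, which is 200 / 4 = 50 complete blocks.

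**1. Allocations that are certain.** A 1:1 block of four has 6 equally likely orders. The observer is assumed to know the block size and to see every earlier allocation in order. An allocation is certain once one arm has used its two places.

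| Position in block | Probability of being certain | Probability of a correct best guess |
|---|---|---|
| 1 | 0 | 1/2 |
| 2 | 0 | 2/3 |
| 3 | 1/3 (first two match) | 1/3 × 1 + 2/3 × 1/2 = 2/3 |
| 4 | 1 | 1 |

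- Certain share: (0 + 0 + 1/3 + 1) / 4 = 33.3%; 200 × 0.333 = 66.7 patients.
- Best-guess accuracy: (1/2 + 2/3 + 2/3 + 1) / 4 = 70.8%.

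**2. One list shared by two hospitals.** Let p be the share of patients at the observer's hospital. The observer sees only that hospital but is assumed to know the place in the block. Position 3 is certain if both earlier patients were at that hospital and match: p² × 1/3. At position 4, two of the first three patients share an arm, and both must have been seen: p². The certain share is (p²/3 + p²) / 4 = p²/3.

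- p = 0.5: 0.25 / 3 = 8.3%
- p = 0.7: 0.49 / 3 = 16.3%
- p = 0.9: 0.81 / 3 = 27.0%

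Simulation gave 8.3%, 16.3% and 27.0%. The values of p are assumptions, because the article gives no site shares. If each hospital has its own blocks, the 33.3% applies again to anyone who sees all of that hospital's allocations.

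**3. Randomly varying sizes.** These figures come from 300 simulated sequences of 200 patients per scheme, with sizes equally likely. The observer sees everything and even knows the set of sizes.

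| Scheme | Certain | Of 200 | Best guess correct |
|---|---|---|---|
| Fixed 4 (exact) | 33.3% | 66.7 | 70.8% |
| 4 and 6 | 5.5% | 11 | 69.2% |
| 4, 6 and 8 | 2.3% | 4.6 | 68.0% |

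Varying the size removes most of the certainty but little of the guessability, because any balanced block rewards guessing the arm that is behind.

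**The case against.** The strongest reply is that the route to bias is inferred. The article does not say who fits the devices, whether enrolling staff see each allocation, whether the coordinators who view step counts also enrol, or whether recruiters knew the block size during enrolment. Publishing it does not settle that. The article condenses a fuller protocol that is not shown and may separate these roles. Eligibility, consent and the baseline walk test are also completed before randomization, which limits selective exclusion once an arm is revealed.

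Most of this stands, and it makes one third a ceiling. It does not remove the point: completing those steps before randomization does not stop someone anticipating the next arm before they begin, and the fixed block size is a rule that the article states, not a detail left out.

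A reader might infer three stronger things that the documents do not support:

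- **That concealment is defeated.** The list stays hidden, and even the best-informed observer is never certain of two thirds of allocations.
- **That assessor masking fails too.** To deduce an arm, an assessor would need a patient's place in the sequence and the arms of others in that block. Nothing in the article gives them either.
- **That 70.8% correct guessing, set against 50%, measures what the fix would gain.** Accuracy remains 68% to 69% under the varying schemes above.

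**Conclusion.** The point holds as a moderate, cheaply avoidable design weakness. Up to one third of allocations, about 67 of 200, are deducible with certainty by someone who knows the block size and sees all earlier allocations in order. For a one-site observer of a shared list who knows the place in the block, the figure is about 8% to 27% over assumed site shares of 50% to 90%. Whether anyone had that knowledge is not documented, and no effect on the walk-test result is shown. The supportable conclusion is that the scheme can undermine the concealment claimed for it. An analysis plan, shown or not, could not repair this afterwards, because predictability is set when patients are allocated.

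**What to change.** Replace the fixed blocks of four with blocks of randomly varying size, for example 4 and 6, or 4, 6 and 8. Withhold the sizes from enrolling staff. Apply this to the whole sequence or, if recruitment has begun, to the part that remains. Withholding the sizes matters because variation alone lowers guessing accuracy only slightly.

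The cost is a setting in the randomization software and a possible small imbalance at the end. At present 200 patients fill exactly 50 blocks. With one list, an unfinished last block could leave the arms apart by at most 3 patients if the largest block is 6, or 4 if it is 8 (half the block size). Against 100 per arm, that is negligible for power.

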### Outcome assessment

#### Primary outcome

The primary outcome is a change in six-minute walk distance that will be measured in a standardized fashion as per the American Thoracic Society Statement 2002 [33]. The initial test will be undertaken during index hospital admission with telemetry monitoring and will be repeated at eight weeks as an outpatient. It will be undertaken by a trained assessor.

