### Statistical analysis

The intervention arm will be compared against the control arm on an intention to treat analysis basis. All statistical analyses will be performed using SPSS v23 (IBM, USA). Baseline characteristics will be summarized using descriptive statistics. Paired Student-t test will be used for all normally distributed continuous variables and will be described as mean with standard deviation. Variables not normally distributed will be analysed using the Wilcoxon Signed Rank test. Categorical variables will be described as frequencies and percentages and will be compared using a Pearson chi-squared test.

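### As described, allocation is not stratified by hospital in a two-hospital trial, so balance within each hospital is not guaranteed; the cost is a small loss of precision, not bias

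*Protocol article*

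**What the plan says.** Under Setting and participants, the protocol article names two sites: "Recruitment will occur during index hospital admission at Monash Medical Centre and Dandenong Hospital". It does not say how the 200 patients will divide between them.

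Under Randomization, patients "will be randomized in a 1:1 fashion", and "A computer-generated table will allocate patients in fixed blocks of four". No stratification factor is given. The same section states that "the allocation sequence will be concealed from the investigators enrolling and assessing patients utilizing computer randomization software", and that "Assessors of the primary outcomes will be blinded to the treatment allocation, however participants are not able to be blinded".

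Under Primary outcome, "The primary outcome is a change in six-minute walk distance". The first walk takes place during the index admission and the second at eight weeks as an outpatient. The site of the second walk is not given.

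Under Statistical analysis, "The intervention arm will be compared against the control arm on an intention to treat analysis basis". The tests named are the paired t-test, the Wilcoxon signed rank test and Pearson's chi-squared test.

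**The concern.** Hospital is the one grouping built into the design. A list in blocks of four balances the arms within a hospital only if each hospital has its own list. If both draw from one list, each block is split between them by order of arrival. Within a hospital the allocation then behaves much like simple randomisation, and blocking secures little beyond equal totals.

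Hospital matters to the primary outcome only if mean change in walk distance differs between the two sites. Case mix, or the timing of the baseline walk within the admission, could produce such a difference. If so, a chance excess of one hospital in one arm moves the estimate in that trial, and the between-hospital variation stays in the residual. As described, neither the allocation nor the named tests deal with this.

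**Working it through.** **Inputs from the protocol article.** Two hospitals; 200 patients, 100 per arm; one table in fixed blocks of four; target 25 m; two-sided alpha 0.05; 76 per arm for 80% power; 101 per arm for 90% power; 20% loss to follow-up.

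**Assumed, because the article does not give them.** The hospital split (50:50 to 70:30) and the difference between hospitals in mean change (5 to 25 m).

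**Step 1: the plan's own sample size.** No SD is stated, so it is solved from the stated numbers with SD = 25 / [(z for alpha + z for power) × √(2/n)].
- 76 per arm: 25 / [(1.960 + 0.842) × √(2/76)] = 55.0 m
- 101 per arm: 25 / [(1.960 + 1.282) × √(2/101)] = 54.8 m

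The two stated sizes agree with each other. 55 m is used below as the total SD.

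**Step 2: imbalance at a hospital under one list.** Let a share p of patients come from one hospital, independently of list position. The arm difference D at that hospital has mean 0 and SD = √[200 × p(1 − p)].

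| Split | SD of D (patients) | P(D is 10 or more either way), exact binomial | Same, simulated |
|---|---|---|---|
| 50:50 | √50 = 7.1 | 17.9% | 17.5% |
| 60:40 | √48 = 6.9 | 17.0% | 17.3% |
| 70:30 | √42 = 6.5 | 14.2% | 14.4% |

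In a separate simulation of 10,000 trials, the difference between arms in hospital share had an SD of 6.5 to 7.0 percentage points under one list, and 95% of trials lay within 13 to 14 points. With a separate list per hospital the SD fell to about 0.7 points.

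**Step 3: shift in the estimate.** Shift = difference in hospital share × hospital difference in mean change. An imbalance of 10 patients at 100 per arm is 10 points. With a 25 m hospital difference the shift is 0.10 × 25 = 2.5 m, which is 10% of the target. At the 95% limit for a 50:50 split, the shift is 0.14 × 10 = 1.4 m for a 10 m difference and 0.14 × 25 = 3.5 m for 25 m. The standard error at 100 per arm is 55 × √(2/100) = 7.78 m.

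**Step 4: precision and power.** With hospital in the model, residual SD = √[55² − p(1 − p) × d²], where d is the hospital difference. Power = Φ(25/SE − 1.960), with SE = SD × √(2/n). For a 50:50 split:

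| d (m) | Variance due to hospital | Residual SD (m) | SE at 80 per arm (m) | Power at 80 per arm | Power at 100 per arm |
|---|---|---|---|---|---|
| 0 | 0% | 55.00 | 8.70 | 82.0% | 89.5% |
| 5 | 0.2% | 54.94 | 8.69 | 82.1% | 89.6% |
| 10 | 0.8% | 54.77 | 8.66 | 82.3% | 89.8% |
| 20 | 3.3% | 54.08 | 8.55 | 83.2% | 90.5% |
| 25 | 5.2% | 53.56 | 8.47 | 83.9% | 91.0% |

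The row d = 0 also gives the power of the unadjusted comparison at any d, because the total SD is held at 55 m. At 80 per arm (100 less 20% loss) the gain runs from about 0.1 to 2.0 points. At 70:30 the power at d = 25 m is 83.6% (80 per arm) and 90.8% (100 per arm).

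**Step 5: consistency check.** At 100 per arm and d = 25 m, the SD of the shift in Step 3 is 0.0707 × 25 = 1.77 m, and 1.77² = 3.1. The adjusted SE is 53.56 × √(2/100) = 7.57 m, so the variances differ by 7.78² − 7.57² = 60.5 − 57.4 = 3.1. The shift is therefore already counted in the unadjusted standard error and is not an extra error on top of it.

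**The case against.** A reader might infer that the comparison is biased by chance. It is not. The expected imbalance is zero, and an unadjusted between-arm test keeps its 5% error rate because hospital variation is part of the SD.

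A reader might also take it as stated that the hospitals share one list, or that the arms will be unbalanced. The shared list is only the natural reading of a singular table in a condensed article; the full protocol may say otherwise. Balance is not guaranteed, which is weaker than saying it will be absent.

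The size also argues for restraint. The outcome is a change score, so a constant difference in course or assessor cancels for a patient tested twice at the same site. The article describes a standardised test, rehabilitation run by one health service and common standard care. A hospital difference of 25 m would equal the whole treatment target, and nothing in the article supports one. Nor is the plan pushed below its stated power: 80 per arm gives 82.0% without adjustment.

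Most of the gain comes from the hospital term rather than from stratification. A covariate is ordinary content for a statistical analysis plan, which is not shown, so its absence from the article is not in itself a fault. Stratified lists bound imbalance among patients randomised, not among those analysed. With 20% loss, dropout alone adds an SD of √(100 × 0.2 × 0.8) = 4 patients to the arm difference at a 100-patient hospital. Separate lists in fixed fours would also be easier to predict in a trial whose participants know their arm.

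All of this stands, and it limits the point to a cheap gain in precision.

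**Conclusion.** The point holds as a minor, optional improvement. As described, hospital is controlled neither in the allocation nor by the named tests, so within-hospital balance is left to chance. The SD of the arm difference is about 6.5 to 7 patients across the splits considered. The consequence is lost precision: under 0.5 points of power for hospital differences up to 10 m, about 2 points at 25 m, and none if the hospitals do not differ.

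These figures rest on an SD of 55 m solved from the stated sample size, on assumed hospital splits and differences, and on the reading that both hospitals draw from one list. No stated figure in the article is wrong on this point, and no passages conflict.

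**What to change.** State whether the list is stratified by hospital. Then:

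1. Analyse change in six-minute walk distance with a between-arm model that includes hospital as a fixed effect. This recovers nearly all of the gain, and it can be done even if recruitment has started on one list.
2. If recruitment has not started, also stratify the randomisation by hospital, using concealed, randomly varying block sizes in place of fixed blocks of four. The varying sizes are part of the fix, because separate lists in fixed fours would make the next allocation easier to guess at each site.

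Stratifying without the hospital term would be incomplete: the unadjusted standard error would not reflect the better balance.

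The cost is one degree of freedom and slightly more work in setting up the lists. No extra patients, visits or staff are needed.
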